## Abstract

**Background:**

We have determined that the impaired accommodation of the lower esophageal sphincter (LES) underlies the pathogenesis of esophagogastric junction outflow obstruction (EGJOO). We have also found that acotiamide may treat EGJOO by improving impaired LES accommodation. The effects of acotiamide in patients with EGJOO need to be further confirmed in a prospective study.

**Methods:**

This trial is a multicenter, randomized, double-blind, placebo-controlled study to compare the efficacy and safety of acotiamide (300 mg/day or 600 mg/day) with those of a placebo in the treatment of patients with EGJOO. The primary endpoint will be the proportion of patients who report an improvement in symptom of food sticking in the chest after 4 weeks of treatment period 1. The secondary endpoints will be the proportion of patients with normalized integrated relaxation pressure (IRP), the value of change from baseline in the distal contractile integral, basal LES pressure, EGJOO–quality of life score, Gastrointestinal Symptom Rating Scale, and the correlation between IRP and each symptom score. During the 2-year trial period, 42 patients from five institutions will be enrolled.

**Discussion:**

This trial will provide evidence to clarify the efficacy and safety of acotiamide as a treatment for patients with EGJOO. Acotiamide might help improve the quality of life of patients with EGJOO and is expected to prevent the progression of EGJOO to achalasia.

**Trial registration:**

This study was approved by the Institutional Review Board (IRB) of Kyushu University Hospital as well as the local IRBs of the participating sites for clinical trials and registered in the Japan Registry of Clinical Trials (jRCT: 2071210072). The registration date is on October 11, 2021.

**Supplementary Information:**

The online version contains supplementary material available at 10.1186/s13063-023-07468-w.

## Introduction

### Background and rationale {6a}

Esophageal motility disorders (EMDs), which include esophageal achalasia, reduce quality of life (QOL) and social labor productivity due to dysphagia and non-cardiac chest pain and threaten life due to aspiration pneumonia in severe cases. High-resolution manometry (HRM), together with the Chicago Classification, has dramatically improved medical treatment for patients with EMDs [1, 2]. Esophagogastric junction outflow obstruction (EGJOO) is a relatively new EMD. EGJOO is characterized by impaired lower esophageal sphincter (LES) relaxation but by intact esophageal body peristalsis, whereas achalasia is characterized by impaired LES relaxation and esophageal body peristalsis. Basic and clinical studies have indicated that EGJOO is a variant or precursor of esophageal achalasia [3]. Importantly, the QOL of patients with EGJOO could be as low as that of achalasia patients owing to dysphagia and noncardiac chest pain. To date, no definitive treatment has been developed for EGJOO. The development of a fundamental treatment for EGJOO is important because problematic symptoms in patients with EGJOO can be improved and the progression of EGJOO to achalasia might also be retarded.

The LES maintains myogenic contractile pressure during the non-eating state to suppress the reflux of gastric contents into the esophagus and pharynx. During swallowing, a rapid and sufficient LES relaxation response is required to transport the bolus to the stomach. We have recently shown that successful LES relaxation is achieved by LES accommodation in combination with swallow-induced LES relaxation [4]. LES accommodation is mainly caused by the physical stimulation of the oral cavity and/or pharynx by liquid and food before the swallowing action occurs [5]. In contrast, swallow-induced LES relaxation results from the swallowing action itself. We have also found that the impairment of LES accommodation but not swallow-induced LES relaxation underlies the pathogenesis of EGJOO, where LES accommodation can be the target for the development of a fundamental treatment for EGJOO.

Acotiamide hydrochloride (acotiamide) (Zeria Pharmaceutical Co. Ltd) has been developed as a gastrointestinal acetylcholinesterase inhibitor [6] and is approved for the treatment of functional dyspepsia (FD) in Japan in 2013 [7]. Acotiamide increases the amount of acetylcholine at the cholinergic nerve ending, which improves the impaired accommodation of the gastric body and fundus and the hypomotility of the gastric antrum in patients with FD. As LES accommodation is induced similarly to gastric accommodation, we hypothesize that acotiamide can be an ideal treatment for patients with EGJOO via the improvement of impaired LES accommodation. Indeed, retrospective and prospective observational clinical studies conducted by the authors have successfully demonstrated the possibility of drug repositioning of acotiamide for EGJOO [8, 9]. However, the efficacy and safety of acotiamide in the treatment of patients with EGJOO need to be further confirmed in a prospective study.

### Objectives {7}

The trial aims to evaluate the effectiveness and safety of acotiamide in the treatment of patients with EGJOO, including the dose-response to acotiamide and a placebo. The hypothesis for the primary endpoint is that acotiamide will improve the symptoms of food sticking in the chest in patients with EGJOO after 4 weeks of treatment compared with a placebo.

### Trial design {8}

The study is an investigator-initiated, multicenter, phase II, double-blind, randomized, placebo-controlled trial with three study arms: acotiamide 300 mg/day, acotiamide 600 mg/day, or a placebo, randomized 1:1:1 and stratified by the institution.

## Methods: participants, interventions, and outcomes

### Study setting {9}

This study will be conducted at five Japanese institutions with experts in the treatment of EMDs: Kyushu University, Kawasaki Medical School, Nippon Medical School, the National Center for Global Health and Medicine, and Gunma University. Participants will undergo 4 weeks of treatment with acotiamide 300 mg/day, acotiamide 600 mg/day, or a placebo. Then, participants without remission of symptoms will undergo another 4 weeks of treatment with acotiamide 600 mg/day. Forty-two patients will be recruited and followed up for a maximum of 10 weeks. The study protocol was written in accordance with the Standard Protocol Items: Recommendations for Interventional Trials (SPIRIT) statement and approved by the Institutional Review Board (IRB) of Kyushu University for Clinical Trials (IRB No. 2021301; June 28, 2021). The trial was registered in the Japan Registry of Clinical Trials (jRCT; No. jRCT2071210072: October 11, 2021) before patient enrollment. All patients participating in the study will give written consent obtained by the researchers. The flow of the study is illustrated in Fig. 1.

**Fig. 1 Fig1:**
[figure not shown]
Schematic of the study design. EGJOO, esophagogastric junction outflow obstruction

### Eligibility criteria {10}

#### Inclusion criteria

The study population will include patients with clinically diagnosed idiopathic EGJOO at study site institutions.

The inclusion criteria will be as follows:Patients with the age of 20 or over at the time of consent.Patients diagnosed with EGJOO by HRM according to Chicago Classification ver 3.0.Patients who have been experiencing a sensation of food sticking in the chest for at least 1 month prior to the time of consent and have a score of 2 (“symptomatic and slightly troubled”) or higher on at least one evaluation of food-sticking symptoms during the screening period.Patients who underwent esophagogastroduodenoscopy and esophagography and in whom other organic diseases that may cause symptoms (e.g., reflux esophagitis, eosinophilic esophagitis, gastric ulcer) were excluded.Patients who understand the contents of the clinical trial and have given written consent of their own free will.

#### Exclusion criteria

Patients meeting any of the following criteria will be excluded:Patients with clinically evident hepatic dysfunction (in whom aspartate transaminase or alanine transaminase levels in the screening period was three times or more than the upper limit of the institutional standard range).Patients with severe renal dysfunction or renal insufficiency (creatinine clearance of less than 30 mL/min in the screening period).Patients with a history of hypersensitivity to any component of the investigational drug.Patients who took acotiamide orally during the month before obtaining consent.Patients with concomitant malignancy. However, patients with completely resected basal cell carcinoma, stage I spinous cell carcinoma, intraepithelial carcinoma, intramucosal carcinoma, or superficial bladder cancer can be included.Patients with frequent irregular dietary habits, such as not eating or binge drinking/eating.Patients with a history of upper gastrointestinal surgery. However, patients who underwent surgeries related to endoscopic treatment, including polypectomy, mucosal resection, and submucosal dissection, will be excluded.Patients who have participated in other clinical trials or clinical studies and used or are using investigational drugs, devices, or products during the 3 months before obtaining consent.Patients with serious cardiac or hematological diseases.Patients with serious drug allergies.Female patients who are pregnant, lactating, or of childbearing potential.Patients who refuse to use appropriate contraceptive methods during the study period.Patients who are judged by the PI or sub-investigator to be ineligible for the study.

### Who will take informed consent? {26a}

Informed consent will be obtained by the PI and sub-investigator using the consent document and consent form before enrollment in the trial. When explaining the trial, the PI or sub-investigator must allow patients to ask questions and provide sufficient time to decide whether to participate in the trial before obtaining consent. Furthermore, investigators or collaborators providing supplemental explanations must answer all questions regarding patient satisfaction.

### Additional consent provisions for collection and use of participant data and biological specimens {26b}

Concerning the collection and use of participant data and biological specimens, possibilities of the secondary use of data and biological specimens will be mentioned in the same consent document as the trial description, which will be explained when signing the consent form. The participant will be deemed to have consented to secondary use as well.

## Interventions

### Explanation for the choice of comparators {6b}

A placebo was used as a comparator in this clinical trial. Administration of a placebo to patients in the control group (*n* = 14) is ethically justifiable because no drug is effective for patients with EGJOO in Japan.

The creation of a placebo intervention is essential for the successful blinding of the participants and research staff. Therefore, Zeria was requested to produce film-coated tablets without acotiamide as placebo tablets. In the placebo group, the placebo will be administered three times a day with two tablets per dose before meals for 4 weeks.

### Intervention description {11a}

#### Pre-treatment observational period

Participants who consented will be examined and observed to confirm their eligibility during the pretreatment observational period. The maximum duration of the pretreatment observational period will be 28 days after obtaining consent. During this period, participants will complete a “symptom diary” for seven consecutive days out of 10 before enrollment. If any of the drugs listed in the concomitant use prohibition had been used, their use will be discontinued after consent has been obtained. After confirmation of eligibility, the participants will be enrolled and randomized 1:1:1 to receive acotiamide 300 mg/day, acotiamide 600 mg/day, or a placebo.

#### Treatment period 1

Participants will take the assigned drugs three times per day before meals for 4 weeks and complete the “application of Medication and Symptom Diary.” Participants will visit the institution after 4 weeks of treatment in period 1 (day 29; validity period: days 28–32) to undergo pre-defined examinations and observations, including HRM and symptom assessment.

#### Treatment period 2

Participants who complete treatment period 1 will take 200 mg/dose of acotiamide three times per day before meals for 4 weeks in an open-label fashion and complete the “application of Medication and Symptom Diary.” Patients will visit the institution after 4 weeks of treatment in period 2 (day 29; validity period: days 28–32) to undergo pre-defined examinations and observations, including HRM and symptom assessment.

However, if IRP is normalized (less than the standard value of IRP set for each HRM instrument) based on the HRM study and the worst value of the symptom of food sticking in the chest is 0 (elimination case) after 4 weeks of treatment in period 1 (day 29; validity period: days 28–32), participants will not proceed to treatment period 2 but will transfer to the post-treatment observational period.

#### Post-treatment observational period

Participants who complete the treatment periods will record an “application of Medication and Symptom Diary” for 14 days after completion of medication. Participants will visit the institution after the 2-week post-treatment observation period (days 15–18) to undergo pre-defined examinations and observations, including symptom assessment.

### Criteria for discontinuing or modifying allocated interventions {11b}

In any of the following cases, the clinical trial for the participants will be discontinued:If investigators conclude that the continuation of the study will be difficult owing to the worsening of the primary disease (such as progression to achalasia).If investigators conclude that the continuation of the study will be difficult because of the occurrence of adverse events.If participants request the discontinuation of the clinical trial or withdraw consent.If performing follow-ups with participants will become difficult owing to reasons such as patients no longer visiting the institution.If the following serious deviations from the study protocol are revealed:If participants’ ineligibility is discovered after enrollment.If participants require or continue the administration of a prohibited concomitant drug.If pregnancy is detected.If investigators conclude that the continuation of the clinical trial will be difficult because of other reasons.

### Strategies to improve adherence to interventions {11c}

To improve adherence to the interventions, the dosing regimen will be simplified, with the same number of tablets and timing of all doses. Before dosing, investigators will instruct patients when to take the medication and what to do if they forget to take it.The investigational drug should be taken before breakfast on the day after the initial prescription.Two tablets of the investigational drug should be taken three times per day before each meal.The dosage of the investigational drug should not be changed based on the patient’s judgment.Medication status (data, time, dosage, and the reason for missed doses) should be recorded in the “application of Medication and Symptom Diary.”Missed doses and the used press-through-package sheet must be kept and brought to the next visit.

The dosing status will be collected using an electronic patient diary, and daily alerts will be set up for patient diary entries.

### Relevant concomitant care permitted or prohibited during the trial {11d}

After obtaining consent, the use of the following drugs will be prohibited until the completion or discontinuation of the clinical trial.Gastroprokinetic agents: mosapride, domperidone, Rikkunshito (Kampo medicine; traditional Japanese medicine), metoclopramide, and itopride.Other investigational drugs.Acotiamide (as a non-investigational drug).Choline stimulants: acetylcholine chloride, carpronium chloride, bethanechol chloride, and aclatonium napadicylate.Cholinesterase inhibitors: donepezil hydrochloride, ambenonium chloride, distigmine bromide, pyridostigmine bromide, and neostigmine.

Endoscopic examinations, except upper gastrointestinal endoscopy during the observational period and gastrointestinal angiography, will be prohibited during the study period.

### Provisions for post-trial care {30}

Participants will not be allowed to continue receiving the investigational drug after the completion of this study. After participation in this study, another treatment deemed optimal for the patient will be selected and provided.

### Outcomes {12}

#### Primary endpoint measurement

The primary endpoint is the proportion of patients exhibiting an improvement in symptoms of food sticking in the chest after 4 weeks of treatment period 1.

“Looking back on your day, did you have any troubles with symptoms of food sticking when you swallowed?” Patients will respond to the question on the following six levels:0: No symptoms1: I had symptoms but had no troubles.2: I had symptoms and had some troubles.3: I had symptoms and was moderately troubled.4: I had symptoms and was quite troubled.5: I had symptoms and was extremely troubled.

The percentage of patients showing an improvement in symptoms is defined as the percentage of patients whose worst symptom score in the latest week was 0 (no symptoms) or 1 (symptoms but no troubles) out of the six levels and whose score improved by at least two points.

#### Secondary outcomes measurement

Follow-up will be performed after 4 weeks of treatment period 1 as a secondary outcome measure.The proportion of patients with normalized IRP on HRM.The value of change from baseline in parameters, including distal contractile integral (DCI) and basal LES pressure (BLESP) on HRM.The value of change from the baseline in the symptom of food sticking in the chest.The value of change from baseline in EGJOO–QOL score (total and each score).The value of change from the baseline in GSRS.The correlation between IRP and each symptom score.

Furthermore, exploratory evaluations after 4 weeks of treatment period 2 will be conducted as a secondary outcome.The proportion of patients showing improvement and the value of change from baseline in symptoms of food sticking in the chest.The value of change from baseline and proportion of patients with normalized IRP on HRM.The value of change from baseline in the EGJOO–QOL score (total score and each score).The value of change from the baseline in GSRS (total and subscale scores).The value of change from the baseline in DCI and BLESP measured by HRM.

Furthermore, the proportion of participants reporting the recurrence of symptoms of food sticking in the chest after 2 weeks of the post-treatment observational period will be assessed.

### Participant timeline {13}

The protocol conforms to the SPIRIT guidelines (Supplemental File 1). The participant timeline during the trial is shown in Fig. 2.

**Fig. 2 Fig2:**
[figure not shown]
SPIRIT flow diagram

### Sample size {14}

The primary analysis will be a comparison of treatment outcomes between the acotiamide (the 300 mg/day and 600 mg/day groups will be pooled) and placebo groups. The secondary analysis will be a comparison of treatment outcomes between the 300 mg/day and 600 mg/day groups to investigate the dose–response to acotiamide. Therefore, the sample size will be set based on a comparison between the acotiamide and placebo groups (allocation ratio 2:1).

In the prospective observational study conducted at Kyushu University Hospital, 10 out of 23 participants (43.5%), who answered the upper abdominal symptom questionnaire (Revised F Scale) after 4 weeks of acotiamide administration (300 mg/day), answered “No” to “Do you feel any symptom of food sticking in the chest (grabbing) when you swallow something?” as a question of the symptoms of food sticking in the chest. Although a scale different from the Revised F Scale will be used to evaluate the efficacy of acotiamide in the current trial, we expect that a similar proportion of patients will show an improvement in symptoms of food sticking in the chest after acotiamide administration. Therefore, we assume that 55% of patients in the acotiamide group will show an improvement in the symptom of food sticking in the chest. In contrast, 15% of patients in the placebo group are assumed to show an improvement in their symptoms. Considering the exploratory nature of this clinical trial, 39 patients are needed to reach a power of 80% for a normal approximation to the binomial distribution with a one-sided significance level of 5%. Considering the possibility of one dropout per group, the target number of participants is set to 42 (14 in each group).

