## Statistical methods

### Statistical analysis methods for primary and secondary outcomes {20a}

The analysis of the primary endpoint will be conducted in the full analysis set, which will include all randomized patients who received at least one dose of treatment during the study, data collected after treatment commencement, and adherence to GCP. A one-sided *p*-value < 0.05 will be considered statistically significant. The following closed testing procedure will be used to compare the three groups: the placebo group as the control group, the group with 300 mg/day acotiamide, and the group with 600 mg/day acotiamide.The placebo and acotiamide groups (300 mg/day and 600 mg/day groups will be pooled) will be analyzed using a normal approximation to the binomial distribution test. If the difference is significant, the next step will be followed. Otherwise, the procedure will be terminated.For the acotiamide groups (300 mg/day and 600 mg/day), a normal approximation to the binomial distribution test will be performed.

In addition, regardless of whether significance is observed in 1 and 2 above, the difference in the proportion of patients who improve between the placebo and acotiamide groups and between the two acotiamide groups, and the two-sided 90% confidence interval will be evaluated.

As secondary endpoints are exploratory endpoints, proportions will be analyzed using a normal approximation to the binomial distribution test with the placebo and acotiamide groups. Similarly, the same method will be used to test the 300 mg/day group against the 600 mg/day group. The change from the baseline will be analyzed using analysis of covariance (ANCOVA) with the baseline values, as covariates will be employed to test with the placebo and acotiamide groups. Furthermore, the same method will be applied to test the superiority of the 600 mg/day group over the 300 mg/day group.

SAS software (version 9.4; SAS Institute, Cary, NC, USA) will be used for all analyses.

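### The 55% acotiamide response behind the 80% power does not follow from the cited 43.5%, at which power is about 56–58% with 39 evaluable patients

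*Protocol article*

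**What the plan says.** The section Sample size {14} of the protocol article bases the calculation on pooled acotiamide against placebo, allocated 2:1. Its evidence is an observational study at one hospital in which 10 of 23 patients (43.5%) on 300 mg/day answered no to a question about food sticking on the Revised F Scale after 4 weeks. The article acknowledges that this trial uses a different scale, but states: "we expect that a similar proportion of patients will show an improvement in symptoms of food sticking in the chest after acotiamide administration". The next sentence is: "Therefore, we assume that 55% of patients in the acotiamide group will show an improvement in the symptom of food sticking in the chest". On placebo it says: "In contrast, 15% of patients in the placebo group are assumed to show an improvement in their symptoms". From these inputs, "39 patients are needed to reach a power of 80" percent at a one-sided 5% level. One dropout per group brings the target to 42.

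The statistical methods section {20a} uses the same level ("A one-sided *p*-value < 0.05 will be considered statistically significant") and a normal-approximation test. Testing stops if the pooled comparison is not significant.

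**The concern.** The premise is 43.5%, the link is similarity, and the conclusion is 55%. The word *therefore* presents 55% as the consequence of the premise, yet it lies 11.5 points higher and no adjustment, target difference or second source is given. This is not a detail that a journal article has merely left to the full protocol: the article sets out its derivation, and the derivation fails as written.

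At stake is what the 80% means. A reader told that the trial has 80% power will take the figure to rest on the earlier study. If the response is close to what that study showed, the chance of passing the first test is much lower. Because {20a} makes the dose comparison conditional on that test, formal testing of dose would be lost with it.

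**Working it through.** **Inputs.** One-sided alpha 5% (z = 1.645); pooled acotiamide : placebo 2:1; rates 55% and 15%; prior rate 10/23 = 0.4348; 39 evaluable (26:13) or 42 (28:14). All are from {14}; {20a} has the same alpha and kind of test. The article does not name the variance estimate. The pooled form is used below because it reproduces the stated number.

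**Formula.** With Δ = p₁ − p₀ and p̄ the weighted mean rate:

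- SE₀ = √[p̄(1−p̄)(1/n₁ + 1/n₀)]
- SE₁ = √[p₁(1−p₁)/n₁ + p₀(1−p₀)/n₀]
- power = Φ[(Δ − 1.645·SE₀)/SE₁]

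**Step 1: the plan's own figure.** At 55% v 15% the required placebo group is 12.5, rounded up to 13, so 13 + 26 = 39. This matches. At 26:13, p̄ = 0.4167, SE₀ = 0.1675 and SE₁ = 0.1390. Power = Φ[(0.400 − 0.2755)/0.1390] = Φ(0.896) = 81.5%. Exact binomial enumeration of the same test gives 81.8%.

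**Step 2: the cited rate, 39 evaluable.** At 43.5% v 15%, Δ = 0.2848, p̄ = 0.3399, SE₀ = 0.1609 and SE₁ = 0.1388. Power = Φ[(0.2848 − 0.2647)/0.1388] = Φ(0.145) = 55.8%. Exact: 58.4%.

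**Step 3: the cited rate, all 42 evaluable.** SE₀ = 0.1550 and SE₁ = 0.1337. Power = Φ[(0.2848 − 0.2550)/0.1337] = 58.8%. Exact: 62.5%.

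**Step 4: sensitivity at 26:13 (formula power).**

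| Acotiamide | Placebo 10% | Placebo 15% | Placebo 20% |
|---|---|---|---|
| 43.5% | 71.7% | 55.8% | 41.2% |
| 50% | 84.5% | 71.3% | 57.0% |
| 55% | 91.5% | 81.5% | 69.0% |

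Exact values for the 43.5% row are 74.5%, 58.4% and 43.2%.

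**Step 5: choice of variance.** With unpooled variance, power at 43.5% v 15% is 65.8% (39 patients) or 68.6% (42), still short of 80%. That form would have needed only 30 patients one-sided at 55% v 15%, so it is not the calculation behind the 39.

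**Step 6: precision of the evidence.** The exact 95% interval for 10/23 is 23% to 66%.

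**Step 7: other pairs of rates at 39.** The same formula gives 82.0% for 44% v 7% (37 points) and 80.7% for 40% v 5% (35 points).

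**The case against.** The strongest reply is that 43.5% is not this trial's response rate. It counts patients with no food sticking at all, on another scale, at 300 mg/day. The primary endpoint also accepts a score of 1, symptoms without trouble, and half of the pooled arm receives 600 mg/day. Moreover, 55% lies inside the interval for 10/23, the trial is phase II and described as exploratory, and a fuller protocol exists that may explain the choice.

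Much of this is fair. The 43.5% should be called the only cited evidence, not the expected rate on the trial's endpoint. But the endpoint is also stricter, since it takes the worst score of the week and requires a gain of at least two points, so the net direction is unknown. If 300 mg/day gave 43.5%, the 600 mg/day arm would need 2 × 55 − 43.5 = 66.5% to bring the pool to 55%, and the article claims no such dose effect. The interval equally includes rates well below 43.5%. Above all, the article gives none of these as its reason: it mentions the change of scale and still expects similarity.

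The missing source for the 15% placebo rate could well be in the full protocol and is not part of this point. It is also fair that the article promises the difference and its two-sided 90% confidence interval whatever the test shows. That gives a reader of a non-significant result something better than the planned power, and nothing in the article says that the 80% will be used for that purpose.

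**Conclusion.** The point holds as a mismatch between the stated basis and the assumption drawn from it. The figure of 80% is right for 55% v 15% but does not follow from the evidence the article cites. At 43.5% v 15% power is about 56–58% with 39 evaluable patients and 59–62% with 42. These figures assume the pooled normal-approximation test, which reproduces the plan's 39, and the plan's own 15% placebo rate.

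A reader might infer more than this, and the documents do not support it:

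- *The sample size is miscalculated.* It is not: 39 and 42 are correct for the stated inputs.
- *Eighty percent power holds only at 55% v 15%, or only for a 40-point difference.* Other pairs with smaller differences reach it too (step 7).
- *The trial will miss a real effect more than four times in ten.* That fits the 39-patient case at 43.5% v 15%. By exact calculation with all 42 evaluable, the miss rate is 37.5%.
- *The true power is 56–58%.* The response rate on this endpoint and dose mix is unknown.

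**What to change.** Change the wording of Sample size {14}, by one of two routes.

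1. Restate the power, for example: *With 39 evaluable patients (26:13), power is about 80% if the response rates are 55% and 15%; at the previously observed 43.5% against 15% it is about 56–58% (59–62% with 42).* Add a short table over acotiamide 43.5–55% and placebo 10–20%, as in step 4.
2. Alternatively, state the basis for 55% on the trial's own endpoint and pooled doses, and remove the sentence expecting a similar proportion.

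The restated sentence should not say that 80% power applies only to a 40-point difference, because that would be wrong.

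No change to the sample size, test, endpoint or conduct is asked for, so the edit is possible with recruitment under way. The cost of the first route is a less favourable stated power; the second needs a justification that the article does not now contain.
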